#### Sample size

As detailed earlier one randomised controlled trial investigating the role of post-operative activity restrictions in outcome following microdiscectomy has recently been reported [7]. The authors recruited 108 patients and noted disc reherniation rates of 11% in the 2-week restriction group and 9% in the 6-week restriction group. Previous studies have indicated a reherniation rate ranging from 2 to 18% [16]. Annual reported reherniation rates have been closer to 4–5% in large series [8, 17, 18]. The authors of the randomised controlled trial calculated it would be necessary to have 800 patients in each arm in order to detect a statistically significant difference in disc reherniation rate and that this may not be feasible. We are in agreement with this assessment.

Reported rates of clinical success for lumbar discectomy vary widely dependent on the criteria. Using the criteria detailed in our composite primary outcome we would anticipate a clinical success rate within the broad range reported in the literature of approximately 70–90%.

In determining the power of this study, we assume that approximately 80% of patients will meet the definition of treatment success. The calculation of sample size can be based upon a threshold of a 20% difference in treatment success as clinically significant (i.e. 80% success vs. 64% success). In order to have 80% power to detect a 20% difference in the binomial outcome of treatment success defined at *p* = 0.05 the sample size calculated would be 78 patients per group. If we allow for an approximately 30% drop-out rate, this will bring the calculated sample size to 105 patients per group for a total of 210 patients in the trial.

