### Outcomes

#### Primary endpoints

While there is no widely used definition of clinical success following lumbar microdiscectomy it is generally accepted that such a definition should take account of outcome measures such as physical function, disability and pain [9–11]. Intervertebral disc reherniation and reoperation are important considerations as potential primary endpoints. In SPORT[12] 20% of patients who underwent surgery rated their progress as less than a major improvement at one year yet only 6% had undergone reoperation. Thus, reherniation and reoperation alone do not account for the majority of unsatisfactory patient outcomes following lumbar discectomy. The use of a composite endpoint allows for the capture of multiple outcomes that influence the overall success of a clinical intervention while also allowing for increased statistical efficiency and efficient resource utilisation [13, 14].

As such the primary endpoint to be assessed in this trial consists of a composite of the following widely accepted outcome measures:18 point reduction in VAS lower back25 point reduction in VAS legs15 point improvement in ODI scoreAbsence of disc reherniation (defined as repeat surgery at the same level)No other secondary intervention (epidural or nerve root injection, medial branch block)

Using the above definitions of treatment success we would anticipate treatment success rates of ~70–90% in keeping with those reported in the literature [8, 15]. This allows the ability to detect a clinically significant difference in outcomes between the two groups (i.e. rates of clinical success) with smaller groups than required for the detection of differences in recurrence rates (i.e. event rate of “clinical success” of approximately 70–90% as opposed to herniation event rate of 5–10%).

Utilisation of the personal wearable electronic device will enable accurate assessment of patient adherence to the allocated post-operative care group.

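### The 80% success rate behind the sample size is not derived for the five-part composite, so the single claim of 80% power is unsupported across the plan's own 70–90% range

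*Protocol article*

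**What the plan says.** The Primary endpoints section lists five elements of success: an 18-point fall in back VAS, a 25-point fall in leg VAS, a 15-point ODI improvement, no repeat surgery at the same level, and no other secondary intervention such as an injection. It does not say in words that all five must be met. For these definitions it forecasts: "we would anticipate treatment success rates of ~70–90% in keeping with those reported in the literature", citing two references whose success criteria are not described.

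The Sample size section repeats the forecast: "Using the criteria detailed in our composite primary outcome we would anticipate a clinical success rate within the broad range reported in the literature". Immediately before, it says: "Reported rates of clinical success for lumbar discectomy vary widely dependent on the criteria". It then fixes the planning value: "we assume that approximately 80% of patients will meet the definition of treatment success". The effect is "a 20% difference in treatment success as clinically significant (i.e. 80% success vs. 64% success", which is 20% in relative terms and 16 points in absolute terms. The result is stated as: "In order to have 80% power to detect a 20% difference in the binomial outcome of treatment success", with 78 patients per group at p = 0.05, raised to 105 per group (210 in total) for drop-out.

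**The concern.** The power of a comparison of two proportions depends on the underlying rate. Here that rate rests only on agreement with a published range, and the plan itself says the range moves with the definition of success. No component rates, correlations or pilot data link the range to this composite.

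The form of the effect adds to the problem. If the difference worth detecting is 20% of the reference rate, it shrinks in absolute terms as the rate falls: 18 points at 90%, 16 at 80%, 14 at 70%.

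The Background section says that finding no difference would let future patients resume normal activity quickly. Failing to detect a real deficit would therefore favour the unrestricted regimen. The plan puts the chance of that failure at 20%, and a reader will take this figure at face value.

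**Working it through.** **Inputs from the Sample size section.** Success 80% vs 64%, 78 evaluable per group, significance level 0.05, power 80%, rate range 70–90%. Allocation is 1:1 (Treatment allocation). Sidedness is not stated; two-sided is used unless noted.

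**Formula.** With p̄ the mean of p1 and p2 (pooled variance under the null, unpooled under the alternative):

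Power = Φ{ [ |p1 − p2|√n − 1.96√(2p̄(1 − p̄)) ] / √(p1(1 − p1) + p2(1 − p2)) }

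**Step 1: the plan's own figure.** For 80% vs 64% at 80% power:

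n = (1.96 × 0.6350 + 0.8416 × 0.6248)² / 0.16² = 3.134 / 0.0256 = 122.4, so 123 per group.

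One-sided 0.05 gives 97. Unpooled, arcsine and continuity-corrected versions do not give 78 either. The figure is approached only under other readings: 80% vs 60% two-sided with unpooled variance (78.5), or non-inferiority with a 16-point margin, one-sided 0.05 and 80% in both arms (78).

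**Step 2: power at 78 per group, 20% relative loss.** √78 = 8.832.

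- 90% vs 72%: (1.5897 − 1.96 × 0.5548) / 0.5400 = 0.930; power 82%.
- 80% vs 64%: (1.4131 − 1.96 × 0.6350) / 0.6248 = 0.270; power 61% (72% one-sided).
- 70% vs 56%: (1.2364 − 1.96 × 0.6828) / 0.6756 = −0.151; power 44%.

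**Step 3: a wider range and both effect scales.** The last column solves the same formula for the difference that has 80% power.

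| Reference rate | Power, 20% relative loss | Power, fixed 16 points | Absolute difference detectable with 80% power |
|---|---|---|---|
| 90% | 82% | 74% | 17.3 points |
| 80% | 61% | 61% | 20.5 points |
| 70% | 44% | 54% | 21.9 points |
| 60% | 32% | 52% | 22.3 points |
| 50% | 24% | 53% | 21.7 points |

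The first three rows are the plan's own range. The last two are assumptions.

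**Step 4: separating the rate from the size of 78.** At 123 per group, which does give 80% power for 80% vs 64%, the relative loss has 95%, 80% and 63% power at rates of 90%, 80% and 70%. The fixed 16-point difference has 91%, 80% and 74%. Correcting the size alone would not remove the dependence on the rate.

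**Step 5: could the composite fall below 70%?** This is illustration only, because the article gives no component rates, and it assumes that all five criteria are required.

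- Three score criteria at 80% and two event criteria at 94%: 0.80³ × 0.94² = 45% if independent, with possible values from 28% to 80% depending on correlation.
- Score criteria at 90% and event criteria at 95%: 0.90³ × 0.95² = 66% if independent. With latent correlations of 0.3, 0.5 and 0.7, simulation gives 71%, 75% and 79%.

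The answer is driven by inputs that the article does not supply.

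**The case against.** The strongest reply is that both sections state the 70–90% forecast for the trial's own composite. It is an open planning assumption with a declared range, and such assumptions are always uncertain. That stands, and it rules out saying that the plan openly used a rate belonging to another endpoint.

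A reader might go further and infer that the cited studies used different criteria, or that the 80% was taken from the statement that "20% of patients who underwent surgery rated their progress as less than a major improvement at one year yet only 6% had undergone reoperation". The documents support neither inference. The criteria of the two studies cited for the range are not shown. The self-rating figure has a different citation and serves a different argument, namely that reoperation alone misses most poor outcomes.

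The effect scale also matters. The Statistical analysis section refers to an absolute delta. With a fixed 16-point difference the fall in power across the range is milder, and with a 20-point absolute difference it is small: at 78 per group, about 78% at an 80% rate and 71% at its lowest, at 60%. This stands as a reason to fix one scale. It does not rescue the stated claim, because the section spells out 80% vs 64%, which is 16 points.

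Finally, the gap between 78 and 123 per group is larger and easier to verify. It is a separate error, and step 4 shows that this point remains once it is corrected.

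**Conclusion.** The point holds as a weakly supported assumption with material consequences. Nothing in the article derives 80% for this composite, and the article itself warns that such rates vary with the criteria. On the stated contrast and the planned 78 per group, power reaches 80% only towards the top of the plan's range. At rates of 80% and 70%, the chance of missing a 20% relative loss is about 39% and 56%, against the implied 20%; for a fixed 16-point loss it is about 39% and 46%.

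These figures assume a two-sided 0.05 test, the normal approximation and 78 evaluable per group. Part of the shortfall comes from the size of 78 and not from the rate.

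It would be tempting to conclude that the composite rate must lie below 70%, with power of 32% or less on the relative scale. The article does not establish that: the all-five rule is implied but not written, and no component rates are given. At high component rates and correlations, a composite rate close to 80% is attainable.

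**What to change.** In the Sample size section, replace the single claim of 80% power with the power of the fixed 210 patients over the plan's own 70–90% range and somewhat lower rates, for example 50–90%. Use one stated effect scale, either relative 20% or absolute 16 points, and give the detectable absolute difference at each rate, as in the table above. State the sidedness and the number of evaluable patients assumed. In the Primary endpoints section, state in words whether all five criteria must be met.

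Add that a non-significant result on the composite will not be read as showing no difference unless the confidence interval for the difference excludes the stated difference.

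This takes a short recalculation and a wording change, with no extra enrolment. The price is a less favourable stated power and a stricter reading of a null result. For example, with 80% success in both arms and 78 per group, the 95% interval extends 1.96 × √(2 × 0.80 × 0.20 / 78) = 12.6 points either side. Excluding a 16-point deficit would then need an observed deficit below about 3.4 points.

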##### Treatment allocation

Patients will be randomised to one of two parallel treatment arms allocated in a 1:1 ratio. Sealed numbered envelopes containing electronically randomised group allocations and group specific post-operative activity instructions will be prepared prior to trial commencement. Following informed consent, a sealed pre-randomised envelope will be allocated by the study nurse to the patient and the patient label affixed to the envelope. The envelope will then be handed to the treating physiotherapist to be opened postoperatively. The study interventions are specifically detailed on this instruction sheet and will be read by the physiotherapist to the patient postoperatively. For both allocation groups, the study card instructions are discussed and reinforced by the treating physiotherapist. The physiotherapist also gives the patient the activity monitor and instructs them on how to use this. The patient will receive a copy of the instruction card to take home and is advised not to disclose their allocation group to medical staff or assessors. The physiotherapist is not involved in subsequent assessment of the patient.

Post-operatively both groups will be fitted with electronic monitoring devices, worn on either the thigh under clothing or carried in the pocket, that will record patient position (sitting/lying/standing) and activity (walking/running/cycling). The devices will be taken off when showering or bathing.

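### 78 patients per group does not give 80% power for 80% vs 64% success; power is about 61% two-sided and 72% one-sided

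*Protocol article*

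**What the plan says.** The Sample size section of the protocol article contains a complete calculation. For the reference rate, "we assume that approximately 80% of patients will meet the definition of treatment success". The effect to be found is a "threshold of a 20% difference in treatment success as clinically significant (i.e. 80% success vs. 64% success". The criterion is "80% power to detect a 20% difference in the binomial outcome of treatment success" at a p-value of 0.05, with no statement of one- or two-sided testing, and the result is that "the sample size calculated would be 78 patients per group". The Treatment allocation section gives equal allocation: "Patients will be randomised to one of two parallel treatment arms allocated in a 1:1 ratio". The enrolment target then follows: "If we allow for an approximately 30% drop-out rate", the number becomes "105 patients per group for a total of 210 patients in the trial".

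Three other sections bear on how this is read. Question and Objectives ask whether unrestricted patients do worse than restricted ones. Hypothesis to be tested says that restriction improves outcomes. Statistical analysis refers back to the sample size section for an absolute delta that will be used to declare equivalence.

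**The concern.** The section uses 20% in two senses. The printed pair, 80% and 64%, is a 20% relative reduction (0.80 × 0.80 = 0.64) and a gap of 16 points. A requirement of 78 per group is what one expects for a gap of about 20 points. The 64% and the 78 therefore do not appear to belong to the same calculation.

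This is the only justification given for the size of the trial. The Background says that if no difference is seen, future patients could resume normal activity quickly. For that use a false negative is the costly error, and the power claim is what readers will rely on to judge its risk. The ambiguity also reaches the equivalence rule in Statistical analysis, because the section it points to leaves both 16 and 20 in play.

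**Working it through.** **Inputs.** p₁ = 0.80, p₂ = 0.64, power 80%, alpha 0.05, 78 per group, 30% drop-out and 105 per group (all from Sample size); 1:1 allocation (Treatment allocation). Sidedness is not given, so both are shown. Normal quantiles: 1.960 (two-sided 5%), 1.645 (one-sided 5%), 0.842 (80% power).

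**1. Trying to reproduce 78 from the printed inputs.** The pooled-variance formula is

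n = [zα·√(2p̄(1−p̄)) + zβ·√(p₁(1−p₁) + p₂(1−p₂))]² / (p₁−p₂)²

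Here p̄ = 0.72, √(2 × 0.72 × 0.28) = 0.6350, √(0.1600 + 0.2304) = 0.6248 and (p₁−p₂)² = 0.0256.

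- Two-sided: (1.960 × 0.6350 + 0.842 × 0.6248)² / 0.0256 = 1.770² / 0.0256 = 122.4, so **123 per group**.
- One-sided: (1.645 × 0.6350 + 0.842 × 0.6248)² / 0.0256 = 1.570² / 0.0256 = 96.3, so **97 per group**.
- Other formulas, two-sided: unpooled 120, arcsine 122, continuity-corrected 135. One-sided: 95, 96 and 109.

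None of these is near 78.

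**2. Power for 80% vs 64%.** Power = Φ{[0.16·√n − zα × 0.6350] / 0.6248}.

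| Evaluable per group | Two-sided | One-sided |
|---|---|---|
| 74 (105 × 0.70 = 73.5, rounded up) | 58.4% | 70.2% |
| 78 | 60.6% | 72.2% |
| 105 (no loss at all) | 73.6% | 83.0% |

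For example, at 78 two-sided: (0.16 × 8.832 − 1.245) / 0.6248 = 0.270, and Φ(0.270) = 0.606. Exact binomial enumeration at 78 gives 61.3% for the two-sided chi-square test and 54.7% for Fisher's test.

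**3. Where 78 could have come from.**

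- *20 points absolute, 80% vs 60%, two-sided.* The unpooled formula gives (1.960 + 0.842)² × (0.16 + 0.24) / 0.04 = 78.5; arcsine gives 81 and pooled 82. Pooled power at 78 is 78.4% for 80% vs 60% and 80.2% for 80% vs 59.5%, so 78 per group detects a gap of a little over 20 points with 80% power.
- *Non-inferiority, both arms truly at 80%, margin 80 − 64 = 16 points, one-sided 5%.* (1.645 + 0.842)² × 2 × 0.16 / 0.0256 = 77.3, so 78. At one-sided 2.5% it is 99.

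The first replaces the printed 64% by 60%. The second keeps both percentages but changes what the 64% means.

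**The case against.** The best defence is the non-inferiority reading. It uses the printed 80%, 64%, 0.05 and 80% power and rounds up to exactly 78, whereas 80% vs 60% gives 78.5 at the lowest. It fits the trial question, which is about inferiority, and it fits the analysis section, which treats the sample size section as the source of a delta. On that reading the 61% would not apply: a true rate of 64% would sit on the margin and be wrongly declared non-inferior only about 5% of the time. The fault would lie in the wording and not in the number.

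Part of this stands. The origin of 78 cannot be settled from the article, 64% may have been meant as a margin boundary, and the 61% depends on a two-sided superiority test. But the text speaks of power to detect a difference, names no non-inferiority margin, and sits beside a hypothesis that restriction is better. The reading also needs two unstated choices, a one-sided 5% test and equal true rates. If it is the true origin, the printed sentence still misdescribes the calculation.

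Unstated sidedness does not rescue the claim, since one-sided power at 78 is 72%. One-sided power passes 80% at 105 per group (83%), but only with no drop-out, against the protocol's own allowance of about 30%. Nor is this a matter of detail left to a fuller protocol: every input is printed, and the result does not follow from them.

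**Conclusion.** The concern holds. As written, 78 per group does not give 80% power to detect 80% vs 64%. Power is about 61% for a two-sided 5% test, the conventional reading and an assumption here, and about 72% one-sided. At the roughly 74 per group left after 30% loss from 105, the two-sided figure is about 58%. The requirement for the stated target is about 123 evaluable per group two-sided, or 97 one-sided, so the shortfall does not depend on sidedness or on the choice among the usual formulas. On the two-sided reading, a difference the protocol calls clinically significant would be missed about four times in ten instead of the stated two in ten. Which calculation produced 78 remains open, and only the sponsor can say.

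**What to change.** Keep the enrolment and correct the statement.

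- Say which design, test, sidedness and difference produced 78.
- If it was a superiority calculation for 20 points, state that 78 evaluable per group gives about 80% power for 80% vs 60% (78.4% by the pooled formula) and about 61% for 80% vs 64%, two-sided.
- If it was a non-inferiority calculation, say so: 16-point margin, 80% success in both arms, one-sided 5%, with 99 per group needed at one-sided 2.5%. The 64% then stays only as the margin boundary, labelled as such.
- In either case drop the phrase that equates a 20% difference with 80% vs 64%, give the difference in absolute points, and use that same delta in Statistical analysis.
- Give the power at the number expected after loss as well. A 30% loss from 105 leaves about 74, not 78; preserving 78 would take 78 / 0.70 = 111.4, so 112 per group.

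The cost is wording in the protocol and SAP and a less favourable stated power. For information only, 80% power for 80% vs 64% two-sided would need 123 / 0.70 = 175.7, so 176 per group and 352 in total. The correction does not depend on recruiting that number.

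### 105 patients per group does not allow for 30% drop-out from a requirement of 78; that needs 112, and 105 covers only about 26%

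*Protocol article*

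**What the plan says.** The Sample size section of the protocol article gives the calculation in two steps. For 80% power at a significance level of 0.05, with success rates given as "i.e. 80% success vs. 64% success", it reports that "the sample size calculated would be 78 patients per group". The second step adds the allowance for loss: "If we allow for an approximately 30% drop-out rate, this will bring the calculated sample size to 105 patients per group". Both groups together make 210, the number that the Abstract also gives, and the Treatment allocation section sets a 1:1 ratio, which matches two groups of 105. The article gives no other drop-out rate and no inflation formula.

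**The concern.** An allowance for drop-out should ensure that the calculated number of evaluable patients is still there after the assumed loss. Here the base, the rate and the inflated size are all stated, and the third does not follow from the first two. A reader who takes the sentence at face value will believe that a 30% loss still leaves the 78 per group on which the power rests. It does not.

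This matters because of the question the trial asks. The Question and Objectives sections ask whether unrestricted patients do worse, and the Background says that finding no difference would let future patients resume normal activity quickly. In that setting lost power makes a null result easier to mistake for reassurance, so the stated loss tolerance should be right.

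**Working it through.** **Inputs, all from the Sample size section**
- Evaluable patients required per group: 78
- Drop-out: approximately 30%
- Planned size: 105 per group, 210 in total
- Success rates: 80% versus 64%; power 80%; significance level 0.05, sidedness not stated

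**Step 1. Try to reproduce 105**
- Standard inflation, n/(1 − d): 78/(1 − 0.30) = 78/0.70 = 111.4, so 112 per group and 224 in total. The plan is 7 per group, or 14 in total, below this.
- The common shortcut, n × (1 + d): 78 × 1.30 = 101.4, so 102. This is not 105, and it would not preserve 78 either (102 × 0.70 = 71.4).
- Standard inflation at 25%: 78/0.75 = 104. This is the round drop-out rate that comes closest to the plan's figure.

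Neither formula gives 105 at 30%.

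**Step 2. What 105 delivers**
- Evaluable at 30% loss: 105 × 0.70 = 73.5 per group, or 147 over both groups. In whole patients that is 73 or 74 per group, 4 to 5 short of 78.
- Largest loss that still leaves 78: 1 − 78/105 = 25.7%.

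**Step 3. Effect on power**

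For a difference in proportions, using the two-sided normal approximation with pooled variance under the null:

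power = Φ{[|p1 − p2| − 1.96 √(2 p̄(1 − p̄)/n)] / √([p1(1 − p1) + p2(1 − p2)]/n)}

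For 80% versus 64%, p̄ = 0.72:
- n = 78: (0.16 − 1.96 × 0.0719)/0.0708 = 0.27, power 60.6%
- n = 73: (0.16 − 1.96 × 0.0743)/0.0731 = 0.20, power 57.8%

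The article does not say which calculation produced 78, so the same comparison is shown under two other readings. Both are assumptions.

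| Scenario | Power at 78 | Power at 73 | Loss |
|---|---|---|---|
| 80% vs 64%, two-sided 0.05 (rates as stated) | 60.6% | 57.8% | 2.8 points |
| 80% vs 60%, two-sided 0.05 (assumed: 20 points absolute) | 78.4% | 75.6% | 2.8 points |
| Non-inferiority, both rates 80%, 16-point margin, one-sided 0.05 (assumed) | 80.3% | 78.0% | 2.3 points |

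The third reading returns exactly 78 for 80% power. Under it, the target is met at 78 and missed at 73.

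**The case against.** The strongest reply is that the rate is given only as approximate, that 105 covers about 26%, and that a gap of some 4 percentage points on a rounded planning guess, costing 2 to 3 points of power, is a matter of wording. The size of the effect is conceded. But an approximate rate excuses rounding, and no rounding of the inflated number turns a 26% allowance into a 30% one. Any loss above 25.7% takes the trial below its own target.

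Three further points have some force:
- **The larger defect lies elsewhere.** For 80% versus 64%, two-sided, the pooled formula needs 123 per group, so most of the distance from 80% power to about 61% comes from the base of 78. This is correct, and none of that distance is counted here.
- **Not every drop-out is lost to the primary outcome.** Repeat surgery or a secondary intervention before loss already fixes a patient as a failure of the composite, and the Non-Adherence section specifies intention-to-treat analysis. That softens the 73, but it does not make 105 the result of the stated allowance.
- **Restating the rate as 25% fits the assumption to the chosen size.** This is fair. That wording should be used only if the investigators consider 25% realistic; otherwise the second option below is the honest one.

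**Conclusion.** The concern holds. On the article's own figures, 105 per group does not follow from 78 and 30%. The correct inflation is 112 per group (224 in total), and 105 covers a loss of 25.7%. At a 30% loss about 73 per group remain, which lowers power by 2 to 3 percentage points under each of the three readings tried.

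The arithmetic on 112, 73.5 and 25.7% needs only the stated figures, and treats a drop-out as a patient without an evaluable primary outcome. The power figures rest also on the assumed sidedness and, in two of the three rows, on assumed rates or margin. The adequacy of 78 is taken as given; if it is too small, this shortfall adds to it.

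**What to change.** Correct the sentence in the Sample size section in one of two ways:

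- Keep 210 and state that 105 per group allows for about 25% drop-out (78/0.75 = 104), if that rate is considered realistic.
- Keep 30% and state that about 73 per group will then be evaluable, giving the power at 73 for the success rates and test actually intended.

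Either costs one sentence and a slightly less favourable statement of loss tolerance or power. Design, conduct and enrolment stay as they are. Keeping both 78 and 30% would instead require 112 per group, 14 more patients in total. If the base of 78 is revised, redo the allowance at the same time as n/(1 − d).
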